***Need to improve pCR rates***

While NACT has the advantage to offer fast-track approval of new drug compounds in oncology, such as the FDA approval of pertuzumab after the Neosphere trial published first in 2012^4^, early expectations of improved survival rates simply by reversing the traditional order of treatments (surgery followed by adjuvant systemic therapy) have not been met^5^. Only recently, however, the Keynote 522 trial could show both a higher pCR rate and an improved event-free survival in TNBC patients receiving the anti-PD1 antibody pembrolizumab, which fuels hopes that specific subgroups will be identified who gain a survival benefit from NACT when compared to standard treatment^6^. Apart from improving outcomes in specific subgroups, NACT facilitates research into post-neoadjuvant systemic treatment strategies, which has already resulted in supplemental therapies such as adjuvant capecitabine in HER2-negative BC^7^ and T-DM1 in HER2-positive BC^8^. It also allows for less extensive surgery by tumour shrinkage and conversion of node-positive BC into node-negative disease, which may be of great benefit for the individual patient in terms of postoperative morbidity and quality of life. Additional systemic drug regimens come, however, at a cost, and associated side effects and toxicities are important to bear in mind. It is therefore utterly compelling to conceive that improved NACT efficacy – and thus de-escalated locoregional therapy – may be achieved by a non-toxic patient-driven life-style intervention such as physical exercise. Such patient empowerment is especially important in the view of the common clinical observation that most patients request to know how they themselves may contribute to a favourable course of their disease and treatment.

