***Physical exercise and chemotherapy***

Physical exercise during chemotherapy is deemed feasible and safe^20^, even when performed via tailored home-based exercise during neoadjuvant chemotherapy^21^. We have evidence from observational studies showing that exercise following a BC diagnosis has a protective effect regarding recurrence, all-cause and cancer-specific mortality^22^. Furthermore, long-term follow-up of a randomized exercise intervention consisting of aerobic and resistance exercise showed enhanced recurrence-free and overall survival in patients with breast cancer^23,24^. In the randomized OptiTrain trial, resistance and high-intensity interval training (HIIT) during postoperative chemotherapy had positive effects on fatigue and muscle strength^25^, muscle mass and function^26^.

Chemotherapy completion at full dosage is strongly associated with an improved prognosis^27^, but dose reductions occur in at least a third of BC patients. Importantly, chemotherapy completion rates can be improved by an exercise program of combined resistance and aerobic training^28^. Physical exercise may thus result in improved pCR rates after NACT not only through proposed systemic anti-inflammatory effects, but also through improved chemotherapy completion rates given at full dosage due to the favourable effects of exercise on fatigue, muscle strength and cardiorespiratory fitness which drive improvements in treatment tolerability. Thus, there is great potential for physical exercise to be put forward as a feasible and effective strategy to support patients to tolerate treatments, which needs to be corroborated in prospective trials.

Physical exercise during NACT and its effects on treatment response and on pCR rates has never been tested. According to clinicaltrials.gov (searched March 22, 2022), there are only two open randomized physical exercise trials in neoadjuvant treatment of BC with oncological outcomes, namely the BENEFIT trial (Germany, N=120) and the Neo-Train trial (Denmark, N=100). Both small trials have the reduction of tumour size through NACT as their primary endpoint. Another trial is registered but not yet recruiting, the NEOLIFE trial (no oncological endpoint, NCT04135586). The Neo-ACT trial goes one step further and explores physical exercise as a means to improve oncological outcomes on a clinically relevant scale.

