3. Overall, breast cancer-specific and recurrence-free survival at 2, 5 and 10 years. For overall survival, censuring is at death or at date for latest follow-up. For breast cancer-specific survival, censuring is at breast cancer-specific death or at date of last follow-up. For recurrence-free survival, censuring is at first local, regional or distant recurrence or at death or date of last follow-up. Contralateral invasive or in situ breast cancer or non-breast secondary malignancies are not counted as an event, in accordance with STEEP criteria^32^.
4. Health-related quality of life including fatigue, assessed by the EORTC QLQ-C30 and BR23 questionnaires (baseline, pre-surgery, 1- and 2-year follow-up)
5. Self-reported physical activity (Modified Godin Leisure Time Physical activity questionnaire) at baseline, pre-surgery, and 1- and 2-year follow-up, facilitating subsequent adjustment for any cross-contamination in the control group
6. Toxicity-related outcomes:
   1. Chemotherapy completion rates, i.e. the proportion of participants receiving the planned number of treatments at full dosage regarding neoadjuvant chemotherapy (measured pre-surgery).
   2. Number of unplanned hospital admissions during neoadjuvant chemotherapy.
   3. Objective cognitive dysfunction measured by an online neuropsychological test (Amsterdam Cognition Scan)^33^ (baseline and 1-year follow-up).
   4. Cardiac toxicity (defined as either left ventricular ejection fraction (LVEF) decline >15% or LVEF decline below an absolute value of 50% or clinical heart failure), to be measured by echocardiogram at baseline and after 3 months of NACT in the HER2-positive subgroup
   5. Sick leave (patient-reported percentage of sick leave as a single measurement pre-surgery and at 1- and 2-year follow-up)
7. Device-measured physical activity level and resting heart rate assessed through the Fitbit activity tracker (baseline to 1-year follow-up).
8. Muscle strength assessed through the handgrip strength test and hypothetical 1-RM maximal leg muscle strength tests (baseline and pre-surgery).
9. Cardiorespiratory fitness assessed by the Ekblom-Bak submaximal cycle test (baseline and pre-surgery).

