An additional analysis, using a dichotomous outcome that classifies patients as *active* and *insufficiently active* based on a score generated from GSLTPAQ, will be performed. Here, a generalized linear mixed model (GLMM) for repeated measures with a logit link function will be implemented. Activity will be assessed at baseline, pre-surgery and at 1- and 2-year follow-up, both within and between treatment arms. An unstructured covariance matrix will be used to model the within-subject error. If the fit of the chosen structure fails to converge, the following covariance structures will be evaluated, in order, until convergence is reached: toeplitz with heterogeneity, autoregressive with heterogeneity, toeplitz, autoregressive and compound symmetry.

1. *Toxicity-related outcomes*

The following toxicity-related outcomes will be assessed: a, chemotherapy completion rates, b, number of unplanned hospital admissions, c, cognitive function (measured at baseline and one year after surgery), d, cardiotoxicity and e, sick leave.

1. Chemotherapy completion rates, i.e. the proportion of participants receiving the planned number of treatments including potential adjuvant chemotherapy, is a dichotomous outcome (yes/no). Both neoadjuvant and adjuvant treatment will be assessed separately (regarded as two independent measurements) in multivariable logistic regression models, adjusting for biological tumour type (stratification factor in the randomization). The treatment effect will be assessed in terms of a resulting odds ratio and a complementary Wald test.
2. For the count outcome number of unplanned hospital admissions, we will use a Poisson regression model, adjusting biological tumour type. If overdispersion is present, a negative binomial regression will be considered instead. Results from the final model (Poisson or negative binomial, whichever fits the data best) will be presented as incidence ratios (IR) together with confidence intervals and a Wald test of the treatment effect.

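### Chemotherapy completion, one of five toxicity-related secondary items, is defined in two conflicting ways, and its adjuvant part compares groups formed after randomisation

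*Protocol*

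**What the plan says.** The endpoint list (Protocol, Outcomes, Variables and measures, secondary endpoint 6, first sub-item) defines completion as "the proportion of participants receiving the planned number of treatments at full dosage regarding neoadjuvant chemotherapy (measured pre-surgery".

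The protocol's own analysis text (Secondary endpoints, Toxicity-related outcomes, item 1) reads: "the proportion of participants receiving the planned number of treatments including potential adjuvant chemotherapy, is a dichotomous outcome (yes/no". It continues: "Both neoadjuvant and adjuvant treatment will be assessed separately (regarded as two independent measurements) in multivariable logistic regression models", adjusted for tumour subtype.

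Other places bear on the choice between the two:

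- Physical exercise and chemotherapy, in the Background, gives as one route to a higher pCR rate "improved chemotherapy completion rates given at full dosage due to the favourable effects of exercise on fatigue", and states that "dose reductions occur in at least a third of BC patients".
- The Study calendar places the recording of toxicity-related outcomes at the pre-surgery visit and leaves adjuvant treatment to routine practice.
- Data management lists type, dose and duration of both neoadjuvant and adjuvant therapy among the eCRF data.
- The Statistical analysis plan section applies intention-to-treat to all outcomes as the main approach.

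**The concern.** Both definitions stand in the protocol itself, so this is a contradiction and not a detail left to a separate SAP. They differ in dosage, treatment phase and time of measurement. Modelling the two phases separately does not remove the conflict, because the dosage question remains inside the neoadjuvant model. The analysis text drops the very condition that links this endpoint to the proposed mechanism. An analyst could follow either section, and the choice could be made after the data are seen.

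The adjuvant model raises a second problem. Whether a patient has an adjuvant chemotherapy plan is settled after randomisation. If that plan depends on response to neoadjuvant treatment, which exercise is meant to improve, the adjuvant comparison mixes any effect on completion with an effect on who is treated. The text gives no analysis set for this model and no coding for patients with no adjuvant chemotherapy planned.

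**Working it through.** **Plan's own figures.** The protocol gives no rate, effect or power for completion. Its only sample size is for pCR (30% v 40%, two-sided 5%, 80% power), and it reproduces: n = [1.96·√(2·0.35·0.65) + 0.842·√(0.3·0.7 + 0.4·0.6)]² / 0.10² ≈ 356 per arm, 712 in total. Nothing below changes it.

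**Step 1: the two definitions side by side.**

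| | Endpoint list | Analysis text |
|---|---|---|
| Number of treatments | as planned | as planned |
| Dosage | full dosage required | no condition |
| Phase | neoadjuvant | neoadjuvant and adjuvant, modelled separately |
| Time | before surgery | adjuvant part can only be known after surgery |
| All neoadjuvant cycles given, dose reduced | not completed | completed |

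**Step 2: size of the gap in the neoadjuvant phase.** Let R be the share with a dose reduction and C the share receiving the planned number. The definitions disagree on patients who received all cycles at reduced dose. That share lies between C + R − 1 and the smaller of C and R. The protocol gives R of at least 1/3; C = 80% to 95% is assumed.

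- Full-dosage completion is at most 1 − 1/3 = 66.7%.
- C = 0.80: gap at least 0.80 + 0.333 − 1 = 13.3 points.
- C = 0.95: gap at least 0.95 + 0.333 − 1 = 28.3 points.
- At R = 1/3 exactly, the gap cannot exceed 33.3 points, and reaches that only if every dose-reduced patient received all cycles.

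**Step 3: adjuvant denominator.** Assume that adjuvant chemotherapy goes only to patients without pCR. At the planned rates this is at most 356 × 0.70 = 249 control and 356 × 0.60 = 214 exercise patients. If 30% to 50% of them receive it (assumed), the numbers are 75 v 64 to 125 v 107.

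**Step 4: coding of non-recipients, all randomised.** Keep that assumption. Let f be the share of non-pCR patients treated and q their completion rate, equal in both arms, so exercise has no effect on adjuvant completion. The odds ratios (OR, exercise v control) are unadjusted.

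- Non-recipients coded as not completed: control 0.70fq, exercise 0.60fq.
- Non-recipients coded as completed: control 1 − 0.70f(1 − q), exercise 1 − 0.60f(1 − q).

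| f | q | Coded not completed | OR | Coded completed | OR |
|---|---|---|---|---|---|
| 0.3 | 0.7 | 0.147 v 0.126 | 0.84 | 0.937 v 0.946 | 1.18 |
| 1.0 | 0.7 | 0.490 v 0.420 | 0.75 | 0.790 v 0.820 | 1.21 |
| 1.0 | 0.8 | 0.560 v 0.480 | 0.73 | 0.860 v 0.880 | 1.19 |

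Over f = 0.3, 0.5, 1.0 and q = 0.7, 0.8, the OR runs from 0.73 to 0.84 under one coding and from 1.17 to 1.21 under the other.

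**Step 5: recipients only.** Split patients into 30% with pCR in either arm, 10% with pCR only with exercise, and 60% without pCR in either. Non-pCR controls are the last two groups (70%); non-pCR exercise patients are the last group (60%). Let the 60% complete at 0.70 and the 10% at 0.70 + d (assumed), with no effect of exercise on completion. Control completion is [10(0.70 + d) + 60·0.70]/70.

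- d = 0: 0.700, OR 1.00.
- d = 0.10: 0.714, OR 0.93.
- d = 0.20: 0.729, OR 0.87.
- d = 0.30: 0.743, OR 0.81.

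With d = 0 there is no bias.

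**The case against.** The best defence is that the neoadjuvant phase has its own adjusted model. That randomised comparison is sound once the dosage wording is settled, and the endpoint list already supplies usable wording. This stands. A reader might infer that the endpoint has no valid result, or that a key endpoint is lost; the documents support neither. Nothing labels this item as key, and it sits within one of nine secondary endpoints.

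A reader might also infer that the adjuvant comparison is, by design, a subset selected by pCR. No section says so. The Background names "supplemental therapies such as adjuvant capecitabine in HER2-negative BC" among the results of post-neoadjuvant research, and the title of the cited T-DM1 trial refers to residual invasive disease. That makes dependence on response plausible, but it is not a stated rule. If adjuvant chemotherapy is given without regard to response, the distortions in Steps 4 and 5 vanish. The analysis set could also be fixed in an SAP that is not shown.

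On size, a gap of 33 points or more does not follow from the protocol's figure. Thirty-three points is the ceiling at exactly one third, and a larger gap needs more frequent reductions. The figure also concerns breast cancer patients in general, not this neoadjuvant population. A gap in the absolute rate is not in itself a bias in the odds ratio between arms.

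Finally, "Both neoadjuvant and adjuvant treatment will be assessed separately (regarded as two independent measurements" could be read as a claim of statistical independence between measurements on the same patients. It more naturally means two separate models. No calculation relies on independence, and the Bonferroni correction holds without it.

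**Conclusion.** The contradiction in the definition is real and rests on the protocol's text alone. Patients who received all neoadjuvant cycles at reduced dose are classified in opposite ways. Full-dosage completion is at most about 67% if the protocol's one-third figure applies to this trial. The two rates differ by about 13 to 28 points or more if completion by number is 80% to 95%, which is an assumption.

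The adjuvant part is weaker evidence. That its groups form after randomisation follows from the calendar. That membership depends on response is an inference. On that inference the odds ratio can fall on either side of 1 according to an unstated coding rule (0.73 to 0.84, or 1.17 to 1.21), and a recipients-only analysis gives 1.00 to 0.81 under the assumed inputs. The bias may be zero.

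The point affects one secondary item. The primary endpoint and its sample size are untouched.

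**What to change.** In the analysis text, replace the definition of completion with the one in the endpoint list: planned number of neoadjuvant treatments at full dosage, assessed before surgery, with all randomised patients as the denominator. Make this the one tested completion endpoint. It agrees with the full-dosage rationale in the Background and with the pre-surgery recording in the Study calendar.

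Report adjuvant completion descriptively, with the number eligible in each arm. If a test is wanted, state its analysis set and how patients with no adjuvant chemotherapy planned are coded, before the data are examined. As an editorial change, describe the two phases as modelled separately rather than as independent measurements.

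The cost is wording only, since the eCRF already holds type, dose and duration for both phases. The downside of the descriptive option is that adjuvant completion is not formally tested.

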| **Endpoints** | The **primary** endpoint is pathological complete response (pCR).  The **secondary** endpoints are:  - Residual Cancer Burden (RCB)  - Objective tumour response (RECIST)  - All-cause, breast cancer-specific, and recurrence-free survival at 2, 5 and 10 years  - Health-related quality of life assessed by the EORTC QLQ-C30 and BR23 questionnaires  - Self-reported physical activity (Modified Godin Leisure Time Physical activity questionnaire)  - Toxicity-related outcomes (chemotherapy completion rates, number of unplanned hospital admissions during NACT, objective cognitive dysfunction (Amsterdam Cognition Scale), cardiac toxicity and sick leave)  - Device-measured physical activity level (Fitbit activity tracker)  - Muscle strength (handgrip strength test and hypothetical 1-RM maximal leg muscle strength tests)  - Cardiorespiratory fitness (Åstrand submaximal cycle test) |
| **Patient selection** | Clinically T1-3, N0-2 breast cancer patients scheduled for NACT and surgery with curative intent.  **Inclusion criteria**:   - Patients with primary invasive breast cancer cT1-T3 cN0-2 - Full tumour biology (ER, PR, HER2, tumour grade, and Ki67) available before initiation of NACT - Oral and written consent - Age ≥ 18 years   **Exclusion criteria**   - Bilateral invasive breast cancer - Pregnancy or breast-feeding - The presence of musculoskeletal, neurological, respiratory, metabolic or cardiovascular conditions that may prevent safe completion of the exercise and testing demands of the trial - Currently performing equal to or more than 150 mins of moderate to high intensity aerobic exercise and 2 sessions per week of moderate intensity resistance exercise |

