## Population

Clinically T1-3, N0-2 BC patients scheduled for NACT and surgery with curative intent and fulfilling all inclusion criteria and no exclusion criteria as listed below. Patients with oligometastases scheduled for such curative treatment are eligible. Baseline stratification is performed based on treating hospital and biological tumour subtype (ER+HER2-, ER+HER2+, ER-HER2+, ER-HER2-) prior to randomization.

Eligible patients are identified at pre-NACT multidisciplinary team conferences and then receive information about the trial by their oncologist or surgeon, avoiding undue delays. Informed consent is mandatory before randomization and can be obtained by physician or nurse with the appropriate delegation. All participants will undergo standardised tests of physical condition and strength before start of NACT and after NACT but before surgery.

| **Inclusion criteria** | **Exclusion criteria** |
| --- | --- |
| - Patients with primary invasive breast cancer cT1-T3 cN0-2 - Full tumour biology available before initiation of NACT (ER, PR, HER2, tumour grade, and Ki67) - Written informed consent - Age ≥ 18 years | - Bilateral invasive breast cancer - Pregnancy or breast-feeding - The presence of musculoskeletal, neurological, respiratory, metabolic or cardiovascular conditions that may prevent safe completion of the exercise and testing demands of the study - Currently performing equal to or more than 150 mins of moderate to high intensity aerobic exercise and 2 sessions per week of moderate intensity resistance exercise (WHO criteria) |

In case of pre-term abortion of NACT, participants may remain on the trial. Participants who have not received at least four treatment cycles (three weekly treatments of e.g. paclitaxel correspond to one treatment cycle) as NACT are excluded from per-protocol analyses (see statistical analysis plan).

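### Unplanned admissions are counted only during chemotherapy with no stated time at risk, so the ratio between arms depends on how long patients stay on NACT, which exercise may change

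*Protocol*

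**What the plan says.** The counting window is set in two places. The Synopsis lists "number of unplanned hospital admissions during NACT", and Outcomes, Variables and measures (toxicity-related outcomes) lists "Number of unplanned hospital admissions during neoadjuvant chemotherapy". Neither gives a calendar window or an end date.

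The model is given under Secondary endpoints, Toxicity-related outcomes: "For the count outcome number of unplanned hospital admissions, we will use a Poisson regression model, adjusting biological tumour type". There is a fallback for the variance: "If overdispersion is present, a negative binomial regression will be considered instead". Results "will be presented as incidence ratios (IR) together with confidence intervals and a Wald test of the treatment effect". No offset, person-time or number of cycles is named.

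Three other statements bear on the length of the window:

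- Population: "In case of pre-term abortion of NACT, participants may remain on the trial". The Statistical analysis plan section makes intention to treat the primary approach for all outcomes. Its per-protocol rule foresees patients who receive less than 40% of planned therapy.
- Physical exercise and chemotherapy: "chemotherapy completion rates can be improved by an exercise program of combined resistance and aerobic training". The same section expects "improved chemotherapy completion rates given at full dosage due to the favourable effects of exercise on fatigue, muscle strength and cardiorespiratory fitness".
- Hypotheses: chemotherapy completion and unplanned admissions are both expected to improve with exercise.

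**The concern.** The window ends with a treatment course whose length is itself a post-randomisation outcome, and the trial hypothesises an effect on a closely related one, completion. Suppose two patients have one admission each, one over a short, abandoned course and the other over about five months. The model as written treats them alike. The arm that stops earlier has less opportunity to accrue admissions.

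The negative binomial fallback deals with extra variance, not unequal observation time. Calling the result an incidence ratio suggests a rate, but no denominator is defined.

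The window may also leave out admissions after the last dose and before surgery, including those of patients who stopped because of toxicity. The Adverse Events section tells investigators not to report NACT-related events, so the admission count is one of the few records of chemotherapy toxicity the trial will hold. At stake is whether a real reduction in admissions would show.

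**Working it through.** **Figures in the plan.** The Protocol gives no figure for admissions: no expected rate, no early-stopping rate and no power. The only design figure used below is the arm size. It reproduces for pCR 30% vs 40%, two-sided 5%, power 80%:

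n = [1.960·√(2×0.35×0.65) + 0.842·√(0.3×0.7 + 0.4×0.6)]² / 0.10² = (1.322 + 0.565)² / 0.01 ≈ 356 per arm, as stated.

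**Step 1: size of the artefact.** Assume the same weekly admission rate in both arms. Let p be the share receiving the full course and f the fraction of the course received by those who stop early. The expected ratio of raw counts (exercise/control) is then the ratio of mean time on NACT:

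R = [p_E + (1 − p_E)f] / [p_C + (1 − p_C)f]

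All p and f are assumptions. For 67% vs 77% with f = 0.4: (0.77 + 0.23×0.4) / (0.67 + 0.33×0.4) = 0.862/0.802 = 1.075.

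| Full course, control vs exercise | R at f = 0.4 | R at f = 0.8 | Rate ratio at which the raw count ratio equals 1 (1/R) |
|---|---|---|---|
| 67% vs 77% | 1.075 | 1.021 | 0.93 to 0.98 |
| 80% vs 90% | 1.068 | 1.021 | 0.94 to 0.98 |
| 90% vs 95% | 1.032 | 1.010 | 0.97 to 0.99 |
| 67% vs 87% (extreme) | 1.150 | 1.043 | 0.87 to 0.96 |

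For the 10-point gains (first two rows) R is about 1.02 to 1.08. With log time on NACT as an offset the ratio is 1.00 in every row, because a constant weekly rate was assumed.

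**Step 2: what it does to the test.** Assume 0.3 admissions per control patient, 356 per arm and Poisson variance. Then SE = √[1/(356×0.3) + 1/(356×0.3×ratio)] and power = Φ(|ln ratio|/SE − 1.96).

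- True rate ratio 0.80, no artefact: SE = √(1/106.8 + 1/85.4) = 0.145, z = 0.223/0.145 = 1.54, power = Φ(−0.42) = 34%.
- Same true effect with R = 1.05: the ratio appears as 0.80×1.05 = 0.84 and power is 23%. With R = 1.075 it appears as 0.86 and power is 18%.
- True rate ratio 0.70: it appears as 0.735 (R = 1.05) or 0.752 (R = 1.075). Power falls from 66% to 54% or 49%.
- No true difference in rate: the two-sided rejection probability is 6.5% at R = 1.05 and 8.4% at R = 1.075, instead of 5%.

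These use a 5% level. The Reporting section prescribes a Bonferroni-corrected level for secondary outcomes, so actual power would be lower throughout.

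**Step 3: when the artefact vanishes or reverses.**

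- If every non-completer has a dose reduction but receives all cycles, R = 1.00.
- If controls who finish have 3 weeks of delay and exercisers 1 week, on an assumed 20-week course: for 80% vs 90%, f = 0.5, R = (0.9×21 + 0.1×10)/(0.8×23 + 0.2×10) = 19.9/20.4 = 0.975. For 67% vs 77%, f = 0.7, R = 19.39/20.03 = 0.968. The bias then favours exercise.

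**The case against.** **The missing offset is silence, not a choice.** The text does not exclude an exposure term, the effect measure is consistent with one, and a separate SAP that is not shown could supply it. The eCRF already records the duration of systemic therapy (Data management). This stands for the offset alone. It does not dispose of the window, which is an outcome definition fixed in the Protocol: an offset for time on NACT would not recover admissions after the last dose.

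**Completion is not duration.** A reader might infer that the Protocol expects exercise to keep patients on chemotherapy longer. No section says so. The outcome definition of completion requires both the planned number of treatments and full dosage, and the only frequency given is for dose reductions (at least a third of patients). A dose reduction need not shorten the course. The analysis text for completion, however, refers only to the planned number of treatments, and on that definition higher completion does mean more cycles. The direction of bias is therefore conditional.

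**The end of the window is not defined.** The Protocol does not say that counting stops at the last dose, and the Study calendar records toxicity outcomes at the pre-surgery visit. Loss of later admissions is thus one reading. That is itself a reason to state the end date.

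**The size rests on assumptions.** The upper figures treat every non-completer as an early stopper who receives on average 40% of the course. A true 10% rate reduction would have only about 12% power at 0.3 admissions per patient even without bias. Both points are correct.

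**Total admissions per randomised patient is a legitimate measure of burden.** It is, but then the window should not close earlier for patients who stop treatment.

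**Conclusion.** The concern holds in a limited form. As written, the count depends on how long each patient stays on NACT, a quantity the intervention may change. If exercise increases the cycles received, the ratio is biased toward more admissions in the exercise arm and a real reduction is diluted.

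A reader might go further and conclude that better tolerance will be scored as more toxicity. The documents do not support that as a general statement. The sign reverses only if the true rate reduction is smaller than the gain in time at risk: 2% to 7% for the assumed 10-point gains, and 13% in the most extreme scenario.

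The inflation of about 1.02 to 1.08 rests on assumed full-course rates, an assumed fraction of the course received by early stoppers, and a constant weekly admission rate. The documents supply none of these. The outcome is one component of one secondary endpoint, and the primary analysis is unaffected. It is worth correcting because correction is cheap and uncounted admissions are harder to recover later.

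**What to change.** Two sentences and one descriptive line:

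- **Outcomes, Variables and measures, unplanned admissions:** define the outcome as the number of unplanned hospital admissions from the first NACT dose to the day before surgery, whatever the number of cycles received, excluding the planned surgical admission. This matches the intervention period in the Intervention section, from start of NACT to surgery.
- **Secondary endpoints, Toxicity-related outcomes:** fit the Poisson or negative binomial model with log(days in that window, ending at death or withdrawal if earlier) as an offset, so that the incidence ratio is a rate ratio with a stated denominator. Name an end date for patients who are never operated on.
- **Descriptive:** show the NACT-only count by arm, with time on NACT.

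The cost is a few more weeks of admissions to record per patient; first-dose, surgery and admission dates should be available from the medical record. Two limits remain. Time to surgery still varies somewhat between patients, and the rate mixes time on and off chemotherapy. An arm that receives more cycles could therefore still have more admissions, but this would reflect treatment received rather than an unequal counting window.
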